### Planned statistical analyses

2.12

The primary analysis will consist of a single planned comparison using a paired t-test to evaluate changes in PPI between 2 mg GT-002 and placebo in patients with SSD. This statistical method allows for a direct assessment of the efficacy of GT-002 relative to placebo in the primary outcome measure. As only one statistical test is performed for the primary endpoint, no adjustment for multiplicity is required. A two-sided significance level of 0.05 will be applied throughout.

Secondary analyses will primarily employ linear mixed models (LMMs) to account for the study design, including multiple drug conditions, various EEG paradigms, and time intervals between measurements. LMMs will enable a comprehensive analysis of both fixed effects (e.g., drug conditions) and random effects (e.g., individual subject variability), thereby providing a more nuanced understanding of GT-002’s impact beyond PPI. This approach will enable direct comparisons between GT-002, oxazepam, and placebo across EEG paradigms. To account for multiple testing in these secondary and exploratory analyses, multiplicity will be controlled using the Holm–Bonferroni method or similar approach.

Exploratory analyses will be conducted to evaluate the impact of factors such as antipsychotic medication type, duration, sex, age, diagnosis, and duration of illness on the acute effects of GT-002 on the EEG paradigms in patients with SSD. Additionally, the differential acute effects of GT-002, oxazepam, and placebo on EEG paradigms and cognition in healthy controls will be assessed using appropriate statistical models. Baseline analyses will be conducted to assess participant characteristics and to facilitate exploratory correlation analyses.

Across all analyses, effect sizes (e.g., Cohen’s d for paired comparisons, partial η² for linear mixed models) with 95% confidence intervals will be reported alongside p-values. Statistical analyses will be performed using R software, and model assumptions (e.g., normality of residuals) will be assessed, with non-parametric alternatives applied as appropriate.

### Biobank

2.13

A research biobank will be established for this trial to store blood samples collected from participants for the measurement of GT-002 plasma concentrations. The samples will be stored at the study site until the end of the data collection, after which they will be transferred to Gabather AB for batch analysis and destroyed immediately following the completion of the analyses. All procedures will comply with relevant regulations, including the General Data Protection Regulation (GDPR) and the Danish Data Protection Act, ensuring ethical handling and disposal of the biological material.

### Data management, storage, and sharing

2.14

All personal data will be handled in full compliance with the General Data Protection Regulation (GDPR) and the Danish Data Protection Act. Patient data will be entered into an electronic Case Report Form (eCRF), depersonalized using subject numbers, and treated as confidential. The project is registered in Privacy, the research registry and of the Capital Region of Denmark (Approval no.: p-2024-15354). The sponsor/principal investigator will allow authorized access to trial data and relevant documents for monitoring, auditing, and inspection by relevant authorities. Upon completion of the TOTEMS trial and following peer-reviewed publication, the full trial results will be provided to Gabather AB in pseudonymized form.

## Anticipated results and discussion

3

The TOTEMS clinical trial will compare the acute effects of GT-002 with those of the widely used benzodiazepine oxazepam, given that both compounds act on the GABA_A_ receptor. The primary and secondary hypotheses are presented in **Table 5**. The expected differences in effect between GT-002 and oxazepam are likely attributable to GT-002’s high-affinity and selective binding to the GABA_A_ receptor, which is currently its only identified high-affinity target, and to its action as a partial PAM. This is in contrast to oxazepam, which functions as a full PAM at the same receptor.

**Table 5 T5:** Description of the primary and secondary hypotheses for both patients with SSD and healthy controls.

Primary hypothesis:
GT-002 will improve/normalize an impaired PPI in patients with SSD, while oxazepam will reduce PPI, and placebo will have no effect on PPI.
Secondary hypotheses:
i) GT-002 will improve/normalize MMN amplitude in patients with SSD, while it will not affect PPI of healthy controls. In both patients and healthy controls, oxazepam will reduce MMN amplitude, and placebo will have no effect on MMN amplitude. i) GT-002 will improve/normalize reduced P300 amplitude and PN in patients with SSD, while it will not affect these parameters in healthy controls. In patients as well as healthy controls oxazepam will reduce P300 amplitude and PN, and placebo will have no effect. ii) Both GT-002 and oxazepam will alleviate the reduction in power and attenuation in phase coherence of the 40-Hz ASSR in patients with SSD. However, GT-002 will assume an intermediate position between oxazepam and placebo. In healthy controls, both GT-002 and oxazepam will increase the power of the 40-Hz ASSR. iii) In both patients and healthy controls, GT-002 will increase alpha band power in resting-state EEG. Oxazepam will increase activity in higher frequency bands (Beta: 13–26 Hz) and reduce the activity of low-frequency waves (by reducing power in Delta (0.5–3 Hz), Theta (3.5–7 Hz), and Alpha bands (10.5–13 Hz). Placebo will have no impact on resting-state EEG. iv) In both patients and healthy controls, oxazepam will impair processing speed, attention, reaction time, and working memory, while GT-002’s acute effects on these cognitive domains will be at the level of placebo.

Schizophrenia spectrum disorders are characterized by considerable neurobiological and cognitive heterogeneity, which poses challenges for detecting pharmacodynamic effects. While enrichment based on specific baseline abnormalities (e.g., PPI deficits or cognitive impairment) could increase sensitivity to particular mechanistic effects, such an approach entails several limitations. First, selectively including patients with abnormal baseline values introduces a risk of regression to the mean, whereby extreme measurements naturally drift toward average levels upon retesting. This could potentially exaggerate apparent treatment effects or mask adverse pharmacodynamic responses. Second, enrichment may introduce a sample bias and reduce external validity, thereby limiting generalizability and potentially obscuring how the compound acts across the broader clinical population.

Evidence from meta-analytic and large multicenter studies supports the presence of robust neurophysiological abnormalities in schizophrenia. Meta-analyses of sensorimotor gating evaluated by PPI [San-Martín et al., 2020 (94)], MMN [Umbricht and Krljes, 2005 (95)], and 40-Hz ASSR [Thuné et al., 2016 (71); Zouaoui et al., 2023 (72)] consistently demonstrate moderate-to-large impairments in patients with schizophrenia compared with healthy controls. These findings were further corroborated by a large multicenter, industry-led study using standardized EEG acquisition and automated analysis pipelines [Cecchi et al., 2023 (96)], which confirmed that patients with schizophrenia exhibit deficits in MMN and 40-Hz ASSR consistent with prior literature. Collectively, this evidence indicates that neurophysiological deficits are prevalent and reliably measurable at the group level in patients with schizophrenia.

In this proof-of-concept trial, we will include the full schizophrenia spectrum, rather than only patients with schizophrenia, to capture the range of cognitive and neurophysiological variability relevant to GABAergic dysfunction, ensuring generalizability and allowing assessment of the overall pharmacodynamic effects of GT-002 in a clinically representative sample. As this is the first trial in a patient population, our main objective is to evaluate how GT-002 modulates early information processing across the full spectrum of schizophrenia-related neurophysiological variability, rather than focusing solely on individuals with marked baseline deficits. The crossover design helps account for interindividual variability, while the inclusion of healthy controls provides an external benchmark for interpreting pharmacodynamic effects. Exploratory analyses will examine whether baseline biomarker or cognitive measures moderate treatment response, thereby informing targeted or stratified approaches in subsequent confirmatory trials.

A potential limitation of this trial is that the sedative effects of oxazepam may be noticeable to some participants. To mitigate this, oxazepam and its matching placebo are both encapsulated to ensure they are visually indistinguishable, thereby preserving blinding and maintaining the integrity of the double-blind design.

While a primary endpoint is a prerequisite in randomized controlled trials, TOTEMS also includes multiple secondary endpoints reflecting other electrophysiological parameters of early information processing. Should the primary endpoint of this Phase II trial prove negative, findings from the secondary endpoints may still justify and encourage further clinical investigation of GT-002.

Although the trial is not designed to directly address CIAS, it aims to determine whether a pharmacological signal on EEG and EMG can be detected following a single dose of GT-002. Positive acute effects would provide preliminary evidence of engagement of the neural circuits underlying hypofrontality, offering a rationale for subsequent repeated-dose trials to evaluate the therapeutic potential of GT-002 as a novel pharmacological approach for alleviating hypofrontality and improving cognitive impairments in patients with SSD. The minor risks associated with trial participation are outweighed by considerable potential future benefits, including clinically significant improvements for patients with SSD and other disorders involving deficient basic information processing. If our hypotheses are confirmed, the trial will provide initial evidence for targeting hypofrontality in schizophrenia, with potential implications for improving treatment and quality of life. Gabather and CNSR will then evaluate initiation of follow-up studies aiming to determine the effectiveness of long-term GT-002 treatment on cognition and symptomatology in patients with SSD. Should a repeated-dose Phase II trial demonstrate efficacy, this would support progression to a larger, international Phase III trial. Ultimately, if development continues to demonstrate efficacy and safety, GT-002 could become globally available, potentially benefiting patients worldwide. Its therapeutic scope may also extend to other disorders where basic information processing is compromised, such as dementia and depression.

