The TOTEMS trial investigates the acute effects of GT-002, a novel GABA_A_ receptor partial PAM that produces minimal potentiation of GABA-elicited Cl^−^ currents, as described in the Investigator’s Brochure (IB), distinguishing it pharmacodynamically from traditional benzodiazepines (**Figure 1**). This limited potentiation may underlie the absence of sedation typically associated with benzodiazepines, while preserving GABAergic enhancement, thereby offering potential for clinical applications. The trial employs a single-dose design to assess whether GT-002 produces measurable effects on EEG and EMG without inducing sedation. Our chosen measures represent sensitive, well-established markers of early sensory and sensorimotor information processing and provide electrophysiological indicators to assess an individual’s level of hypofrontality. Acute changes in these measures may indicate engagement of neural circuits underlying hypofrontality, providing an initial signal of potential therapeutic effects. From an ethical perspective, initiating a single-dose design in this first patient trial is appropriate, as it allows preliminary pharmacodynamic evaluation while minimizing exposure. While this single-dose trial does not directly target cognitive impairments in patients with SSD, measurable effects on EEG and EMG following single dosing would provide necessary preliminary pharmacodynamic evidence to justify subsequent repeated-dose trials aimed at evaluating potential improvements in CIAS or broader cognitive function.

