The Personal and Social Performance Scale (PSP Scale) evaluates four domains: socially useful activities, personal and social relationships, self-care, and disturbing and aggressive behaviors (110, 111). Each domain is rated using a 6-point severity scale based on a structured clinical interview, resulting in a total score ranging from 1 to 100, where higher scores indicate better functioning. The PSP is administered to patients only at screening to assess social and personal functioning, and ratings are based on the participant’s functioning over the past month.

An adapted version of the Visual Analog Mood Scale (VAMS) is used to assess eight specific mood states: Afraid, Confused, Sad, Angry, Energetic, Tired, Happy, and Tense. Each mood is rated using a horizontal visual analog scale, anchored with a “neutral” descriptor at the left end and the target mood descriptor at the right end. Respondents mark the point along the scale that best represents their current emotional state. Scores range from 0 to 100, with 100 indicating the maximal intensity of the mood and 0 indicating minimal intensity or absence of that mood. The VAMS is administered to all participants repeatedly throughout each study drug exposure day (prior to study drug administration, before the EEG/EMG battery, prior to the cognitive test battery, and following completion of testing) to sensitively detect acute mood fluctuations and potential sedative effects during each study drug exposure day.

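### Table 5 predicts no effect of GT-002 on several outcomes, but section 2.12 describes only difference tests and sets no margin for supporting those predictions

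*Protocol article*

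**What the plan says.** Table 5 (section 3) contains predictions of no effect beside predictions of change. For four cognitive domains (attention, reaction time, working memory, processing speed), in both groups, it says that GT-002's "acute effects on these cognitive domains will be at the level of placebo". For P300 amplitude and PN it predicts improvement in patients, "while it will not affect these parameters in healthy controls". The mismatch negativity (MMN) row has a similar clause, "while it will not affect PPI of healthy controls", although the rest of that row concerns MMN amplitude. For the placebo condition, the primary hypothesis says that "placebo will have no effect on PPI".

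Absence of sedation appears as an aim of the single-dose design in the Introduction: "to assess whether GT-002 produces measurable effects on EEG and EMG without inducing sedation". Section 2.9 gives the Visual Analog Mood Scale (VAMS) the task "to sensitively detect acute mood fluctuations and potential sedative effects during each study drug exposure day".

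On inference, section 2.12 gives a paired t-test for the primary endpoint, linear mixed models for the secondary analyses, unspecified suitable models for EEG and cognition in controls, and Holm–Bonferroni or a similar method for secondary and exploratory tests. It adds: "A two-sided significance level of 0.05 will be applied throughout". It also promises effect sizes with 95% confidence intervals for all analyses. Section 2.11 sizes both groups to detect a difference: d = 0.70 for patients (18 needed, 20 planned) and d = 0.55 for controls (28 needed, 30 planned).

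**The concern.** A test for a difference can show that GT-002 differs from placebo. When it fails to do so, that is weak evidence that the two are alike, especially with 20 or 30 people. The article gives no equivalence or non-inferiority test, no margin, and no other criterion for calling a no-effect prediction supported. Holm adjustment guards against false claims of difference; for a prediction of no difference it works the other way, because it makes non-significance more likely.

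What is at stake is the contrast with oxazepam. The article presents GT-002 as non-sedating and, in Table 5, as sparing cognition where oxazepam impairs it. Section 3 says what would follow if the hypotheses were confirmed, but not when a hypothesis of no effect counts as confirmed. Without a rule fixed in advance, a modest real effect and a true absence of effect could be described in the same words.

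**Working it through.** **Inputs.** n = 20 patients and n = 30 controls, two-sided α = 0.05, planning effects d = 0.70 and 0.55 (sections 2.11 and 2.12). The article gives no margins and no size for the Holm family. The margins below, and a family of four (one test per cognitive domain), are assumptions. All effects are in SDs of the paired difference.

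**1. Reproducing the plan's figures.** Power of a paired t-test comes from the noncentral t with n − 1 degrees of freedom and noncentrality d√n.
- n = 20, d = 0.70: 0.70 × √20 = 3.13, power 84.4% (plan: about 84%).
- n = 20, d = 0.65: 78.7% (plan: about 79%).
- n = 18, d = 0.70: 79.9%, so the stated 18 is right to rounding; strictly, 19 passes 80%.
- n = 28, d = 0.55: 80.1%, which matches the stated 28. With n = 30 it is 82.9%.

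**2. Chance of a non-significant result when GT-002 has a real effect** (1 − power). The strictest Holm step over four tests uses 0.05 / 4 = 0.0125.

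| True d | n = 30, α 0.05 | n = 20, α 0.05 | n = 30, α 0.0125 | n = 20, α 0.0125 |
|---|---|---|---|---|
| 0.30 | 64.5% | 75.3% | 82.7% | 89.7% |
| 0.40 | 43.7% | 60.3% | 66.4% | 80.3% |
| 0.50 | 24.6% | 43.5% | 46.3% | 67.1% |

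**3. What the promised intervals can show.** The expected 95% half-width is about t(0.975)/√n: 2.045/√30 = 0.37 SD and 2.093/√20 = 0.47 SD. Even an observed difference of exactly zero would leave effects of that size open.

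**4. What an equivalence rule could achieve.** Two one-sided 5% tests amount to requiring the 90% interval to lie within ± the margin m. Simulated power when the true difference is zero:

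| Assumed margin (SD) | n = 30 | n = 20 | N for 80% power |
|---|---|---|---|
| 0.30 | 5.5% | 0.9% | 97 |
| 0.40 | 38% | 12% | 55 |
| 0.50 | 70% | 39% | 36 |
| 0.55 | 80% | 53% | 30 |
| 0.70 | 97% | 83% | 19 |

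Hand check with 2Φ(m√n − t(0.95)) − 1: for n = 30 and m = 0.55, 3.01 − 1.70 = 1.31, giving about 81%; for n = 20 and m = 0.70, 3.13 − 1.73 = 1.40, giving about 84%. Both agree with the simulation.

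A non-inferiority rule looks at the harmful side only and is somewhat easier to meet. At one-sided 5% and the same two margins, its power is about 90% (n = 30, m = 0.55) and 91% (n = 20, m = 0.70).

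**The case against.** A reader might infer that the investigators will treat a non-significant p-value as confirmation. No sentence says so, and the point does not depend on it: what is established is that no criterion is given.

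The strongest defence is that section 2.12 commits to effect sizes with 95% intervals in every analysis, that margins for non-primary outcomes are often left to an analysis plan (not shown here), and that Table 1 lists cognition, EEG effects in controls and tolerability as exploratory. This stands as to weight. It does not remove the mismatch between the form of the stated hypotheses and the stated tests, because an interval supports sameness only against a margin. Table 5 also calls the same hypotheses secondary.

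The cognitive hypothesis also has two parts: oxazepam impairs while GT-002 does not. Data too noisy to show anything would also miss the oxazepam effect, so the active arm gives some check on sensitivity. That is fair, and it means the percentages above apply to one GT-002 versus placebo test and are not the chance that the whole hypothesis appears confirmed. Yet a visible oxazepam effect does not rule out a smaller GT-002 effect.

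Three further readings go too far:
- *Absence of sedation is a tested hypothesis.* It is a design aim and is not in Table 5.
- *A finding of no cognitive effect would be the ground for repeated dosing.* The Introduction and section 3 tie that step to measurable EEG and EMG effects.
- *The placebo prediction cannot be tested at all.* Section 2.7 describes the EEG/EMG and cognitive batteries only after dosing, but the schedule figures are not shown and section 3 mentions baseline measures, so a pre-dose recording cannot be ruled out.

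**Conclusion.** The point holds as a mismatch between hypothesis and method for the no-effect predictions in Table 5. For a single unadjusted comparison, a real effect of d = 0.30 to 0.40 would be non-significant 44–65% of the time with 30 controls and 60–75% with 20 patients, and more often after Holm adjustment. The planned numbers give about 80% power to exclude only effects of about 0.55 SD (n = 30) or 0.7 SD (n = 20).

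These figures rest on a paired t-test as a proxy for the mixed model, no dropout, a true difference of zero for the equivalence power, and assumed margins and Holm family. A claim covering all four domains together would have lower power than any single one.

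The primary comparison, its α and its sample size are untouched. This is an inexpensive improvement and not a must-fix.

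**What to change.** 1. Before the first unblinding, which section 2.4 places after analysis of the healthy controls' data, set an equivalence or non-inferiority margin for each no-effect outcome, in the test's own units and with a reason. Conclude that GT-002 is level with placebo only if the 90% interval for GT-002 minus placebo lies within the margin; otherwise report the result as inconclusive.
2. Where no margin can be justified, reword the hypothesis as an expectation to be reported by estimate and confidence interval.
3. Apply the same rule to the VAMS item Tired if a claim of no sedation is to be made.
4. State that 30 controls and 20 patients give about 80% power to exclude only about 0.55 and 0.7 SD of the paired difference.
5. Describe placebo as the reference condition instead of predicting that it has no effect, since the text describes no pre-dose EEG/EMG or cognitive measurement.
6. Reconcile the MMN row of Table 5, which names PPI as the outcome in controls, so that it is clear which no-effect prediction is meant.

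The cost is wording in Table 5 and section 2.12 plus the work of justifying margins; no new data are needed. The price in interpretation is that small true effects, and often a true absence of effect under a tight margin, will be reported as inconclusive.
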